### Intervention

Participants in both intervention groups will receive twelve 2-h training sessions over a 4-week period, resulting in a three sessions/week pattern. A pragmatic window will be set to ensure for each participant the execution of all 12 sessions in a maximum of 5 weeks, to accommodate possible withdrawal of one or more sessions (e.g., intercurrent illness, sudden family problems, etc.). Patients who miss more than three consecutive training sessions will be dropped out from the study. If a participant misses a training session, the physiotherapist will inform the research coordinator and will contact the patient by phone, to determine reasons for missing and to motivate them to take part to the next scheduled training session.

The first training hour will consist of the specific training scheduled for each group (gait training), whereas the second training hour will be common to both groups. In detail, an experienced physiotherapist will perform lower-limb and core stretching exercises to increase muscle flexibility as well as strengthening exercise for the lower limbs. The second training hour will be carried out over the entire duration of the study by the same physiotherapist, treating two participants contemporaneously, to ensure the same exercises for all patients to avoid possible confounding factors and bias during the results interpretation.

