### Randomization and blinding

After the collection of the informed consent and of the baseline data, the physician responsible for the enrollment will create the allocation sequence, on a personal password-protected computer. The password to log into the allocation list will be given only to the research coordinator, to the physician who created it, and to the administrator responsible of randomization. Then patients will be randomized to one of the two groups by the external administrator not involved in the trial to prevent selection bias through a computerized randomization stratification approach. Participants will be stratified by their degree of impairment (EDSS score) to obtain a balance between groups regarding the baseline physical capacity. The randomization scheme (1:1 ratio) will be set up in permuted blocks of 4 to ensure a similar number of participants between groups. Finally, the subjects will be assigned to one of the two treatment groups: RAGT (experimental group) or CT (active control group). The participants cannot be blinded to the two interventions as the two training protocols were detailed in the informative form for the patients given during the screening visit. Once randomized, patients cannot change the treatment assigned for any reason (e.g., participant request), but in case any medical conditions derived from that specific treatment develop, the training will be immediately suspended. Outcome measure assessors who have to remain blind to group allocation will not have access to the randomization list. Unblinding will not be permissible for these researchers. All outcome data will be recorded on two different electronic spreadsheets by two blinded researchers involved in the trial, and the accuracy of the data will be checked by the research coordinator for all the outcome measures. The privacy of the participants and their personal medical records will be guaranteed by treating the data according to the Italian Law n. 196/2003, to the “Safe Harbor Act” (2000/520/CE) and to the “European Union Data Protection Directive (95/46/EC 24 October 1995).”

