### Outcome assessment and data collection

Outcome measurements will be evaluated at the Operative Unit of Physical and Rehabilitation Medicine of Ferrara University Hospital by the same blinded assessors at the four time points (Fig. 1): (a) baseline (prior to the first intervention session, T0), (b) intermediate (after six training sessions, T1), (c) end of treatment (after the completion of 12 sessions, T2) and (d) follow-up (after 3 months from the end of training program, T3). Before the last outcome assessment, a blinded physiotherapist will contact each participant to remind them to attend the measurements sessions. A summary of the measures to be collected is reported in Table 1. A physician member of the research team involved in the subject enrollment will administer the MMSE and all the other clinical measures (EDSS, MAS) to determine eligibility for each patient. Moreover, the person responsible for the participant selection will record the general demographic information (age, gender), comorbidities and medical history.

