### Sample size and power

The primary outcome for this study is to detect walking differences (specifically, T25FW measurement) between MS subjects who underwent RAGT and MS subjects who underwent CT. To calculate the sample size for this study, we used the data from a previous study [18] where a RAGT effect size of 0.40 was observed. This value is based on a decrease of values for T25FW from 8.8 ± 3.1 s at baseline to 7.4 ± 3.8 s after RAGT. Given equal allocation between treatment and control arms, 88 subjects are required to maintain a Type I error rate of 5.0 and 80% power to detect a difference between intervention groups. Conservatively, we expect a 10% rate of dropout or loss to follow-up. We will assume that dropout participants will not improve from the last measured point; thus, the sample size will be increased by 10% to 98 subjects (49 per arm).

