### Intention-to-treat

All analyses will be conducted using intention-to-treat, where any subject randomized to one arm remains in that arm regardless of whether or not they received the intervention. Missing values, though we will make any effort possible to reduce their incidence, will be treated using the multiple imputation procedure, considered one of the best methods to handle missing data [83]. Moreover, a sensitivity analysis that assesses the stability of the study’s conclusions, comparing intention-to-treat analysis to an analysis that takes into account level of participation in the intervention arm, will also be performed.

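### The dropout rule and a session-based T2 lose outcomes after randomisation, so the intention-to-treat analysis leans on imputation for data that could have been observed

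*Protocol article*

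**What the plan says.** - **Intervention.** Twelve sessions are given at three a week over four weeks, with a window that allows "the execution of all 12 sessions in a maximum of 5 weeks". Then: "Patients who miss more than three consecutive training sessions will be dropped out from the study".
- **Outcome assessment and data collection.** T1 follows six sessions. T2 is "end of treatment (after the completion of 12 sessions, T2") and T3 is "follow-up (after 3 months from the end of training program, T3"). No assessment is tied to time since randomisation or since the first session.
- **Intention-to-treat.** All analyses are by intention-to-treat, where "any subject randomized to one arm remains in that arm regardless of whether or not they received the intervention". Missing values "will be treated using the multiple imputation procedure". A sensitivity analysis compares this with an analysis by level of participation in the intervention arm.
- **Sample size and power.** The 88 subjects required are raised to 98 for 10% dropout or loss to follow-up, with the statement: "We will assume that dropout participants will not improve from the last measured point".
- **Randomization and blinding.** If the assigned treatment causes a medical condition, "the training will be immediately suspended". Leaving the study is not mentioned there.
- **Selection criteria.** One exclusion criterion covers relapse, a change of disease-modifying or symptomatic drugs, or any other confounder arising while the study runs.

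**The concern.** Intention-to-treat needs two things: patients stay in the arm to which they were randomised, and their outcomes are collected whatever treatment they received. The plan promises the first and works against the second. Dropping non-attenders from the study ends their measurement because of something that happened after randomisation. Attendance may depend on the arm, on how the patient is doing, or on both, and participants are not blinded. The primary comparison could then reflect who stayed as well as what the treatment did. An outcome that was not measured at the time cannot be recovered later.

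**Working it through.** **1. The plan's own figure.** 88 / (1 − 0.10) = 97.8, so 98 randomised (49 per arm). The stated total reproduces. The expected loss is 0.10 × 98 = 9.8, about 10 patients from all causes. The article does not say how many of these the missed-session rule would produce.

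**2. Follow a patient who misses four sessions in a row.** The Intervention rule drops this patient from the study. Twelve sessions are not completed, so the T2 condition is not met. T3 is counted from an end of training that is not defined for someone who stops early. T0 exists, because baseline precedes randomisation. T1 exists only if six sessions were done first. The Intention-to-treat section still counts the patient, so T2 and T3 have to be imputed.

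**3. Follow a patient who misses four sessions, never more than three in a row.** Five weeks at three sessions a week gives 5 × 3 = 15 slots, and 15 − 4 = 11 sessions. The dropout rule does not apply and the patient is still in the trial. Unless extra sessions are fitted into a week, 12 sessions are not reached within the window and T2 is again undefined. The session-based T2 is therefore a problem of its own, separate from the dropout rule.

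**4. The participation sensitivity analysis.** It needs outcomes across the range of attendance. The dropout rule removes patients at the low end.

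**5. Is dropping from the study just loose wording for stopping training?** The Randomization and blinding section speaks of suspending training only, so the article uses both terms. The literal reading of the Intervention rule cannot be dismissed, and the sections need reconciling.

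**6. What keeping these patients does to power (illustration under assumptions).** The calculation starts from the effect that 44 per arm detects with 80% power, two-sided 5%: d = (1.96 + 0.8416) × √(2/44) = 0.597. The article's 0.40 is not used because it is a within-arm pre-post value and, as a two-arm difference, would need 99 per arm; that is a separate matter. Power is approximately Φ(d × √(n/2) − 1.96), with n per arm.

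| Situation | n per arm | d | Power |
|---|---|---|---|
| All 98 measured, full effect | 49 | 0.597 | 84.1% |
| 10% removed and not analysed | 44.1 | 0.597 | 80.1% |
| All 98 analysed, 10% with no between-arm benefit | 49 | 0.9 × 0.597 = 0.538 | 75.8% |

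The last row is a pessimistic case, since a patient who stops early may keep gains made before stopping. The table describes power only. It says nothing about bias, for which the document gives no inputs.

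**The case against.** A reader might infer that intention-to-treat cannot be carried out at all. The documents do not support that. Every randomised subject stays in the assigned arm, T0 is available for all and T1 for some, and multiple imputation is planned. Imputation can use arm and the observed T0 and T1 values, so it does not simply hand dropouts the results of completers. The rule is also narrow: it needs more than three consecutive missed sessions, and the plan provides a five-week window and telephone contact after a missed session. Nor does the article say that early stoppers go unmeasured at T2, and visit details of that kind are often left to the full protocol.

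Most of this stands and limits the claim. Two things remain. The dropout rule is stated, not omitted, and it contradicts the intention-to-treat statement. Imputation in standard form assumes missing at random, and here the missingness follows from adherence and is created by the protocol itself. Imputation is the right tool for outcomes that could not be obtained. It is a weak substitute for outcomes that could have been.

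**Conclusion.** The contradiction holds. As written, the dropout rule and the session-based T2 lose primary-outcome data after randomisation in patients selected by adherence, and the intention-to-treat result would depend on imputation for them. The scale is bounded only loosely, by the expected loss of about 10 of 98 from all causes. Whether the comparison would be biased, in which direction and by how much depends on attrition by arm and on the outcomes of those lost. The document gives neither; equal losses with equal outcome gaps in both arms would cause no shift.

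Two stronger readings should not be adopted. A reader might infer that patients who relapse or change drugs are withdrawn after randomisation. The exclusion criterion can be read that way, but no section states withdrawal or deletion of data, so it is an ambiguity to resolve. A reader might also see a conflict between assuming no improvement after the last measurement and using multiple imputation. The first is a planning assumption for the sample size and the second an analysis method; they are poorly aligned but do not strictly contradict each other.

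**What to change.** Reconcile the Selection criteria, Intervention, Outcome assessment and Intention-to-treat sections:

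1. Separate stopping training from leaving follow-up. When training stops is for the investigators; a patient who stops stays in the study for measurement unless consent is withdrawn.
2. Set T1, T2 and T3 at calendar times from the first session for every randomised patient, whatever the number of sessions: T2 at the end of the existing four-to-five-week window and T3 three months later.
3. State that the relapse, drug-change and confounder criterion decides eligibility before randomisation. Later events are recorded and the patient's data retained.
4. Keep multiple imputation for what is still missing, and use no improvement from the last measured point as a sensitivity analysis.

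**Cost.** Changes of wording, and follow-up of roughly 10 patients at visits already scheduled. Analysing non-adherent patients may dilute the effect; in the illustration, power falls to 75.8% if 10% show no between-arm benefit. The trial is listed as recruiting, so patients already dropped may be past a calendar T2. The change protects mainly those still to be measured.

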### RAGT experimental group

Patients included in this group will perform RAGT on the Lokomat treadmill (Hocoma AG, Volketswil, Switzerland). During these sessions subjects will wear a harness attached to a system to provide body weight support and they will walk on the treadmill with the help of a robotic-driven gait orthosis. The legs are guided according to a physiological gait pattern. The torque of the knee and hip drives can be adjusted from 100 to 0% for one or both legs. The speed of the treadmill can be adjusted from 0 km/h to approximately 3 km/h and body weight support from 0 to 100%. During the first session, these training parameters will be set according to subject characteristics and demand level. As training progresses, adjustments in the assistance provided by the driven gait orthosis (guidance), the amount of body weight support and treadmill speed will be performed. Training sessions will last for an hour with 30-min of real walking time because subject setup in the device takes approximately 30 min. At the end of each session the total meters walked, the average walking speed and the percentage of body weight support from 0 to 100% will be tracked.

### Active control group (CT)

Patients included in the CT will focus their efforts on gait training. During the 1-h individual physiotherapy sessions, patients will perform assisted over-ground walking for a total of around 40 min, inserted between a 10-min warm-up and cool-down period. The patient will be encouraged by the same experienced physiotherapist to walk back and forth on an 80-m indoor flat corridor with their habitual walking device (crutches, rollator). Every patient will be asked to walk without stop until reaching an effort corresponding to a value of 8 out of 10 of the Borg Rating of Perceived Exertion Scale [58]. When that given intensity has been reached, the patients will be allowed to rest sitting on a chair; after a suitable rest period, sufficient for the patient to return to values of 1/10 of the scale, the training will restart following the procedures previously reported. At the end of each session, the total meters walked, as well as the effective walking time, will be recorded on a properly developed module.

### Concomitant care and recommendations

During the 4-week period of in-hospital training, patients will be asked not to undertake other physiotherapist treatments. Moreover, patients will be asked to wear the same shoes and orthosis during all the testing and training sessions.

### Intervention fidelity and monitoring of adverse events

Before the beginning of the study, treatment physiotherapists will be trained by a member of the research team with a high level of experience in RAGT and CT training of MS patients. Physiotherapists will be provided with 1:1 guidance focused on the treatment’s characteristics and peculiarities, and their ability to complete training sessions will be verified. When the study begins, to each physiotherapist will be given the module to record the specific training administered to each participant. During the whole duration of the study, the members of the research team and research coordinator will randomly visit training sessions, to ensure that the scheduled intervention is being performed accurately and with high adherence to the protocol proposed. Any adverse unpredictable event will be recorded in the registry of each patient and the electronic database of the study, and managed according to the policies of the hospital, with referral for appropriate medical follow-up.

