### Laboratory-based measures

#### Samples processing (harvesting and storing)

Circulating biomarker analyses will be performed on blood samples collected from patients at each time point (T0, T1, T2 and T3), in fasting conditions, at the University Hospital of Ferrara. Blood collection will consist of a total of approximately 18 ml of whole blood distributed in three different test tubes (based on the analyses to be performed) containing either ethylenediaminetetraacetic acid (EDTA) or sodium citrate or ribonucleic acid (RNA) stabilizer. Once a suitable vein has been identified, the area where the needle will be inserted will be sterilized and the needle inserted. When the amount of blood extracted satisfies the study requests, the needle will be removed from the vein and a swab will be placed on the forearm. The patient must remain in a resting position for few minutes and they will be asked to communicate any adverse reaction felt. The blood samples collected will be labeled with a unique alphanumeric code identifying each participant; samples will be then packed and safely transferred to the Biobank Service of the Laboratories of the Technologies of the Advanced Therapies of the University of Ferrara. Samples collected in EDTA will be processed in real time for rare circulating cell population quantification through multiparametric flow-cytometry analyses. Samples collected in sodium citrate will be centrifuged and plasma will be collected, aliquoted and frozen at −80 °C in multiple and single-use aliquots for analysis of soluble circulating factors. Samples collected in RNA stabilizer will be used for analysis of transcriptional expression profiles. The biological samples of the participants will be catalogued and stored anonymously using the unique alphanumeric code identifying the patients, the access to samples will be restricted to the researchers involved in the RAGTIME trial.

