### Data monitoring and interim analysis

The RAGTIME trial, dealing with well-established and safe rehabilitation procedures, paralleled by a rigorous handling of potential harms as a local hospital policy, expects to minimize all the potential risks. Moreover, this being a single-center study, a Data Monitoring Committee will not be required. The research coordinator will be in charge of the interim analysis (with statistician support) and for taking the final decision to stop, modify or terminate the trial. Eventual possible modifications or amendments to the protocol will be discussed within the research group and communicated by the research coordinator to the funding body for approval or refusal. An interim analyses performed by the scientific experts of the funding body will be scheduled after 18 months from the beginning of the trial. It will consist of a compilation of an interim evaluation checklist form, of a study interim report form and a public preliminary data presentation and discussion. Once the trial is concluded, the research coordinator will be responsible for the final dataset, and will state the number of research team members who can have access to the data collected.

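### The only stated rule for entering adverse events in the study database is worded for an undefined class of unpredictable events, so capture of foreseeable training-related harms is not assured

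*Protocol article*

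**What the plan says.** The section on intervention fidelity and monitoring of adverse events states: "Any adverse unpredictable event will be recorded in the registry of each patient and the electronic database of the study". The same sentence goes on to say that these events are "managed according to the policies of the hospital, with referral for appropriate medical follow-up". The rule makes no distinction between robot-assisted training and conventional therapy.

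Three other places bear on harms from training:

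- Randomization and blinding: "in case any medical conditions derived from that specific treatment develop, the training will be immediately suspended".
- Intervention: after a missed session the physiotherapist informs the research coordinator and phones the patient "to determine reasons for missing and to motivate them to take part to the next scheduled training session".
- Data monitoring and interim analysis: the trial's procedures are described as safe and "paralleled by a rigorous handling of potential harms as a local hospital policy". The next sentence states that "a Data Monitoring Committee will not be required".

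One further statement concerns blood sampling only. Under samples processing, patients rest after the draw and "they will be asked to communicate any adverse reaction felt".

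**The concern.** A rule for recording adverse events normally covers all of them, and whether an event was expected is then one attribute of the record. Here expectedness is part of the entry condition, and the term is left undefined. A therapist or coordinator who follows the text literally could leave out a problem that is a known possibility of the training, because it was not unpredictable.

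The two arms expose patients to different things: a harness and driven orthosis on a treadmill in one, and over-ground walking to 8 out of 10 on the Borg scale in the other. Any foreseeable harms could therefore differ between arms, and these are the events that the qualifier may exclude.

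There is also a link to the efficacy data. A suspension of training could become more than three consecutive missed sessions, at which point the patient is dropped from the study. Missing values are then handled by multiple imputation. Whether that imputation is reasonable depends partly on knowing why data are missing. If the cause was a foreseeable harm, nothing in the article requires the cause to be in the database.

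**Working it through.** No arithmetic applies. The point rests on the wording of a rule, and the article states no adverse event rate from which a loss could be computed. The check was to read every place that mentions adverse events, harms, reactions or suspension of training, and to ask two questions of each. Does it send events to the study database? Does it cover foreseeable events from training?

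1. **Intervention fidelity and monitoring of adverse events.** Database entry: yes. Foreseeable training events: not on a literal reading, because the rule is worded for *unpredictable* events. The section also mentions a form on which each physiotherapist records the training given. No adverse event item on it is described.
2. **Randomization and blinding.** Database entry: not stated. Foreseeable training events: it provides for conditions caused by the assigned treatment, but says only that training is suspended.
3. **Intervention.** Database entry: not stated. Foreseeable training events: captured indirectly at best, through the phone call about a missed session. A harm that causes no absence would not trigger the call.
4. **RAGT experimental group and Active control group.** The items listed for each session are metres walked, average speed and body weight support in the first, and metres walked and walking time in the second. No harm item is listed.
5. **Samples processing.** Patients are asked about any reaction, with no qualifier, but this concerns the blood draw and not the training. Database entry is not stated.
6. **Data monitoring and interim analysis.** Harms are referred to local hospital policy. No rule on what enters the study database is given.

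Only the first place answers yes to the first question, and it carries the qualifier. None of the others extends the rule to foreseeable training-related events. The rule for treatment-derived conditions (item 2) and the recording rule (item 1) do not contradict each other, since such a condition might also be judged unpredictable and so be recorded. But the text does not ensure this.

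**The case against.** The best defence is that the adjective is not meant as a technical limit. The article's English is not always idiomatic, and an adverse unpredictable event may simply mean something untoward and unplanned. In that sense an individual fall or injury is unpredictable even when its type is well known. The article never contrasts expected with unexpected events and lists no foreseeable harms. The full protocol, the case report forms and the hospital policy are not shown, and a journal article condenses such material. These arguments stand as limits on the point. They do not remove it, because the article does state the rule and qualifies it with a word it leaves open.

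A reader might infer more than the document supports:

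- *Only unpredictable events are recorded, and foreseeable ones will be lost.* The text contains no such exclusion. The most that can be said is that foreseeable events may go unrecorded.
- *The arms cannot be compared on safety.* One rule covers both arms, so whatever is recorded can be compared. The comparison may be incomplete, which is different from impossible. It is also not among the stated aims or outcomes.
- *Suspended training will appear as unexplained missing data.* The phone call after a missed session makes this unlikely as a general statement. The gap is that the article does not say the reason obtained is entered in the database.
- *The trial goes without a monitoring committee because harms are rigorously handled.* The reason attached to that decision is the single-centre setting. The sentence on harms supports a different claim, that risks will be minimised.

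Severity grading, assessment of relatedness and tabulation by arm may reasonably be left to the full protocol or the analysis plan. Their absence here is no finding.

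**Conclusion.** The point holds in a limited form. The one database rule for adverse events that the article shows is worded for an undefined class of events. On a literal reading it does not require entry of foreseeable training-related harms, including treatment-derived conditions that suspend training. Harm records, and any safety comparison between arms, may therefore be incomplete.

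The size cannot be given. It depends on how staff read the word and on event rates that the document does not report. If they already record every adverse event, nothing is lost in practice and only the text needs correcting. The conclusion assumes that no other document, such as the full protocol or the hospital policy, overrides the wording shown.

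This is a minor point and does not affect the primary analysis of gait speed as planned. It deserves correction because it is nearly free, and because without a monitoring committee the final decision to stop or modify the trial lies with the research coordinator, who needs complete harm records.

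**What to change.** Delete *unpredictable* from the recording rule. The sentence should then require that every adverse event in either arm, expected or not, is entered in the patient's registry and the study database, including any event that leads to suspension of training. If the authors did mean to restrict entry to a particular class of events, they should define that class and say where the remaining events are recorded.

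The change concerns documentation only and leaves the handling of events and the rules for suspending training as they are. It costs one word in the protocol and slightly more recording work for the therapists, who already complete a form for the training they give.
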